[figure not shown]

#### A3a. Financial Conflict of Interest

Does any member of study personnel (Investigator (including investigator's spouse and/or dependent children)) that are involved in the design, conduct, or reporting of the research have a Significant Financial Interest (SFI) that would reasonably appear to be affected by the research for which funding is sought and/or associated with an entity/business that would reasonably appear to be affected by the research?

No

### Section Ab: General Information

#### A5. Funding Source:

Organization: VA HSR&D

**A7. Research Category:****A8. Therapeutic Intent**

Does this trial have therapeutic intent?

Yes

**Section B: Exempt Request****B. Exempt From IRB Review**

Not Applicable

**Section C: Background Information**

Co-occurrence of diabetes and clinically significant depressive symptoms is highly prevalent, with grave consequences for quality of life and health. Almost one third of diabetic patients have clinically significant symptoms of depression. They use health services more, experience greater functional impairment, and have higher morbidity and mortality than diabetic patients without depression. Furthermore, depression is associated with greater non-adherence to diabetes self-care. Due to the complex interrelation between diabetes and depression, patients need focused interventions that blend physical and emotional health strategies and interface through existing clinical-care settings, such as VA Patient Aligned Care Teams (PACT).

Provision of comprehensive care for diabetes and depression in primary care is limited due to system-, provider-, and patient-related barriers, exacerbated in rural settings due to limited availability of providers (especially mental health specialists), patient concerns about mental health treatment, and logistic issues, such as distance to VA services. Our prior work suggests that the interrelation of diabetes and depression provides an opportunity to treat both simultaneously, using individualized behavioral coaching to activate goal setting and positive behaviors (e.g., adhering to medication regimens, managing diet, and increasing pleasant events). Our intervention involves telephone interactions to increase access for Veterans residing at significant distances from a VA facility. In this proposal, behavioral activation describes intervention content, founded on behavior-change techniques using goal setting and action planning. Behavioral coaching describes the intervention, which uses non-expert providers (coaches) to implement treatment.

Approximately 3 million Veterans live in rural areas and have numerous health-related challenges, including lower health-related quality of life, more comorbidities, and limited access to health care services than their urban or suburban counterparts. Rural-dwelling veterans with diabetes and depression are typically treated in community-based outpatient clinics (CBOCs). Therefore, to be effective, treatment modalities for veterans must meet the demands of community-based care. This is especially true for patients who reside in rural settings where medical and psychological services are scarce and difficult to obtain. These conditions are not well managed in rural areas due to various barriers to care, including distance/ transportation, limited health care supply, quality of health care, financial constraints, and social isolation. Diabetic patients in rural areas tend to have more problems controlling their blood sugar, blood pressure and cholesterol compared to urban

patients, thereby increasing their risk of diabetic complications. Similarly, rural patients with depression have similar barriers to care that increase their risk of poorer health outcomes as well.

Current methods of treating diabetic patients with depression require the use of clinical services that are difficult to access outside of tertiary care centers. Access to certified diabetes educators, nutritionists, and mental health clinicians is limited in community-based and rural settings. Too little commitment has been given to the application of blended behavioral therapies that target the physical and emotional health needs of patients with diabetes and depression in CBOCs. Furthermore, these interventions may be more effective if they utilize methods that can better reach rural-dwelling Veterans such as home-based and telephone mediated therapeutic sessions. Training and utilizing behavioral health coaches (BHCs) to deliver telephone-mediated therapies may enhance the reach of treatments for co-occurring diabetes and depression. The implementation of such treatments will require the development and testing of therapeutic manuals and BHC training protocols to ensure standardization and effectiveness.

## Section D: Purpose and Objectives

The overall objective of this study is to improve the effectiveness of care for Veterans with diabetes and depression receiving care in VA community-based outpatient clinics (CBOCs) or living at some distance from tertiary care. Given our experiences, we do not believe that effectiveness can be achieved simply through dissemination of research findings to PCPs or CBOCs using standard channels. The current proposal has obtained funding to integrate our prior work which developed methods for conducting a behavioral coaching intervention including training coaches to administer a standardized treatment protocol, and measuring the development of high-quality behavioral goals and action plans. Our prior work, which included pilot data for the proposed HOPE study, demonstrated that behavioral coaching interventions can improve clinical outcomes in patients such as: lowered HbA1c levels, reduced depressive symptoms and relieved physical and emotional symptoms. For the current proposal, we enlisted the use of the RE-AIM (reach, effectiveness, adoption, implementation, maintenance) framework, a hybrid evaluation model of the real-world impact of health behavior interventions that provides an evaluative framework for measuring effectiveness of complex, behavioral interventions. Using this model will allow us to assess the effectiveness of the HOPE intervention, while also allowing us to address potential barriers to implementation.

Specific aims are:

1.) To compare at 6 and 12 months the clinical effectiveness of HOPE enhanced primary care with that of education enhanced primary care (EUC).

Hypothesis 1a: After 6 months' active treatment, HOPE will produce greater improvements than EUC in diabetes (shown by glycated hemoglobin [HbA1c] levels) and depression (shown by PHQ-9 scores).

Hypothesis 1b: At 12 months (following a 6-month maintenance phase), HOPE participants will continue to show significantly greater improvements than EUC patients in HbA1c and depression symptoms.

Exploratory Aims

2.) To examine the role of potential moderators and mediators on intervention effectiveness. Exploratory Aim 2a. To evaluate factors that mediate or moderate effectiveness at 6 and 12 months for all enrolled patients. Potential mediating and moderating variables include patient-level (diabetes distress and self-efficacy and sociodemographics) and facility-level (availability of mental health services) factors. Exploratory Aim 2b. To evaluate factors that mediate or moderate effectiveness at 6 and 12 months for patients in the HOPE arm. Factors include adherence (e.g., session attendance), fidelity (ratings of coach effectiveness), and treatment implementation (e.g., goal-setting quality and self-management behaviors).

3.) Evaluate the potential for embedding HOPE in VA primary care settings, using the RE-AIM framework for evaluating effectiveness of behavioral interventions. Exploratory Aim 3a - Reach. Compare clinical and demographic characteristics of participants with those of all potentially eligible patients. Exploratory Aim 3b - Adoption. Qualitatively elicit PACT clinician and participant perceptions of HOPE to prepare for implementation next steps.

## Section E: Protocol Risks/Subjects

**E1. Risk Category**

Category 1: Research not involving greater than minimum risk.

**E2. Subjects**

Gender:

Both

Age:

Adult (18-64 yrs), Geriatric (65+ yrs)

Ethnicity:

All Ethnicities

Primary Language:

English

Groups to be recruited will include:

Healthy, non-patient, normals; Patients

Which if any of the following vulnerable populations will be recruited as subjects?

Employees or lab personnel

Vulnerable populations require special protections. How will you obtain informed consent, protect subject confidentiality, and prevent undue coercion?

To guard against any undue influence or coercion by the study on the administering institution's employees, the consent process will emphasize the voluntary nature of the research by including the following statements in the consent form: Participation in this study is voluntary and will not affect your current or future employment status. There is no penalty for refusing to participate and you may withdraw your participation in the study at any time. Additionally, your identifying information and any opinions, insights or information you share will be kept strictly confidential.

**E3. Pregnant woman/fetus**

Will pregnant women and/or fetuses (as described in 45 CFR 46 Subpart B) be enrolled in the research?

No

**E4. Neonates**

Will neonates of uncertain viability or nonviable neonates (as described in 45 CFR 46 Subpart B) be enrolled in the research?

No

**E5. Children**

Will children be enrolled in the research?

No

**Section F: Design/Procedure****F1. Design**

Select one category that most adequately describes your research:

z.r) Randomized, Efficacy Study -- Surgical Techniques/Interventions

Discuss the research design including but not limited to such issues as: probability of group assignment, potential for subject to be randomized to placebo group, use of control subjects, etc.

We propose a randomized clinical trial to compare the effectiveness of HOPE with that of enhanced usual primary care (EUC) for distance-based Veterans with comorbid diabetes and depressive symptoms receiving

primary care services at the VA. Randomization will occur at the patient level and be stratified by clinical site. In addition, we will evaluate the durability of the treatment over a 6-month period following the active-treatment phase. To better understand the mechanics of change, we will conduct an exploratory examination of the mediating and moderating variables associated with changes in the primary outcomes (HbA1c levels, depression symptoms) at both 6 and 12 months. Additional exploratory analyses will attempt to better understand the relative strengths, weakness, barriers, and facilitators important to future implementation if the intervention produces significant changes.

The proposed study will enroll 242 patients with diabetes and depressive symptoms who receive care in VA CBOCs throughout Southeast Texas, as well as MEDVAMC patients living >20 miles from the hospital who face similar distance related treatment barriers. 60% of the participants (n=146) will be randomized to receive 9 behavioral coaching sessions in 6 months (active intervention), followed by 6 months without coaching (maintenance period); the other 40% (n=96) will receive EUC, which will include the provision of educational materials and feedback about diabetes and depression. All consented participants (both treatment arms) and their PCPs will be notified of the diabetes control and depressive symptoms and provided with guideline-based recommendations for treatment of depressive symptoms. Randomization will be stratified by clinical site.

#### Inclusion Criteria:

Patient inclusion criteria consist of: (a) a diagnosis of diabetes mellitus; (b) an average HbA1c level >7.5% in the prior 12 months; and (c) clinically significant symptoms of depression. Verification of diabetes mellitus diagnoses will be based on data collected from the VA data warehouse. To verify that participants meet the depression criteria, we will use participant self-report of clinically significant depressive symptoms according to the PHQ-9, where a score of greater than/equal to 10 on the PHQ-9 will signify a clinically meaningful symptom burden.

Coach inclusion criteria consist of: (a) being a VA primary care clinician; and (b) being willing and able to commit to at least 7 months of participation in the study, including training and seeing patients.

#### Exclusion Criteria:

We will exclude potential participants only for clinical factors that would render a telephone-based behavioral activation intervention inappropriate. Specific exclusion criteria are: (a) lack of regular access to a telephone; (b) significant cognitive impairment (three or more errors) on an established six-item screening exam; and (c) meeting criteria for bipolar, psychotic, or substance-abuse disorders; (d) presence of hearing impairment; (e) their medical chart recommends not titrating therapy due to prior history of significant hypoglycemic events; or (f) they live within 20 miles of the MEDVAMC. Patients will be secondarily excluded if their HbA1C level falls below 7.5% at baseline assessment, or if they report suicidal ideation on the PHQ-9 at baseline assessment.

Patients receiving mental health services for conditions other than bipolar, psychotic or substance-abuse disorders at the time of study recruitment will not be excluded. All mental health treatments and health service-use characteristics will be included in study analyses as covariates.

Coaches do not have any exclusion criteria. All disciplines in primary care are invited to participate.

## F2. Procedure

**Consenting Clinicians:** Before training, interested clinicians will sign the 10-1086 form with study RAs. Consent is necessary as we intend to publish this data. Coaches will act within their regular duties and will not provide any PHI, but will contribute data about the process/experience and implementation of the research.

**Training and Evaluating Coaches:** Coaches may/may not be mental health clinicians, but have a basic background in behavioral sciences. Training will use a 2-step process, involving dedicated workshop-style sessions and ongoing consultation+feedback. Specific procedures include: clinician manual-guided instruction, modeling and role-playing, and regular feedback about ongoing cases. Workshop training sessions will be standardized by the study PIs and occur prior to coaching. Feedback will be structured around the ACE scales developed for the project (Sect S). Oral+written feedback will be offered (form attached in Sect S). Training materials and procedural support will also be made available on an ongoing basis through study website- <http://www.vaprojecthope.org/>. Access to For Coaches section will be password protected. Data collection from Coaches: Coaches will complete 4 surveys (Sect S) about the process/implementation of the intervention in their clinical setting. Coaches will be assigned an ID#, and the link between ID and names will be stored on a password-protected M drive folder accessible only to study staff not involved in data analysis. Data will be collected using IDs at 4 times: before training workshop, after

training workshop, after feedback with study staff (~6mos post-workshop), at exit from the study. Coaches also complete 2 surveys about experience with each veteran (Sect. S, WAI-C and CEC-C) to be administered ~4 mos. after assignment. Survey responses will be entered into a fillable form on a password protected M: drive folder accessible to study staff and coaches (a separate folder from that which contains ID-name link). No PHI or sensitive data will be entered. Once complete, surveys will be entered by staff into a database on the M drive for analysis. Identifying Patient Participants: The study sample will be identified and enrolled using a multi-step screening process. An initial pool of eligible patients with diabetes will first be identified by VISN 16 Data Warehouse and randomly assigned as potential participant lists stratified by clinical site. Information/PHI to be used in this initial data pull that may identify a subject include name, address, phone #, year of diabetes dx and the dates/values of most recent A1c. This info will be used to determine poor glycemic control as an inclusion criterion and to contact the subject to complete the next steps in the screening process. Birth date, race, ethnicity, and gender will also be collected in the initial data pull as descriptive statistics to determine if there are statistically significant differences between interested and not interested patients. The location of the patient's PC facility and their doctor's name will be collected in the initial data pull to identify subjects to guide randomization and coach pairing after randomization respectively. A waiver of informed consent/HIPAA authorization has been approved by the IRB on 2/15/2012 for this initial step of the screening process (Sect S). We will take all measures necessary to ensure the confidentiality/anonymity of all participants. Patients who meet criteria for uncontrolled diabetes and geographic location will receive an opt-out letter about the study. Patients who do not opt out will be contacted by study personnel for the second step of the multi-step screening process. Study RAs will then use a structured, phone-based screening interview to identify patients who preliminarily meet our depression inclusion criteria on the abbreviated PHQ-8 scale. The screening interview will also exclude from that group who screens positive on the PHQ-8 but for whom a phone-based intervention would be inappropriate. Specific procedures and measures to be administered can be found in HOPEIIR Screening Procedures (Sect S). After completing the detailed screening, patients who still meet eligibility will be approached for informed consent and a baseline assessment. The PHQ-9, as part of the baseline assessment, will serve as the final eligibility check in this multi-step screening procedure. Following the phone screening, interested and preliminarily eligible patients will be mailed a copy of the ICF w/out signature lines, along with the baseline measures. After the patient has time to review these docs, study staff will call the patient on the phone to go over the informed consent process. The patient will have the opportunity to ask questions and must demonstrate an understanding of the risks and benefits of participation before verbal consent to participate is achieved. After consent, the subject will begin the baseline assessment. Because this intervention will be used in the medical care of participants, subject's participation in this protocol will result in their medical records being flagged. The following Title 38 U.S.C. 7332 protected information will be collected for scientific research purposes as part of this research protocol: drug and/or alcohol abuse. This info will be maintained in accordance with the security requirements of 38 CFR Section 1.466, or more stringent requirements. This info will not be re-disclosed except back to the VA. This info will not identify any individual patient or research subject in any report of the research, or otherwise disclose patient or research subject identities. The purpose of collecting alcohol and or drug abuse and treatment info (38USC7332) is to conduct scientific research. No personnel involved, in this study, will identify, directly or indirectly, any individual patient or subject in any report of such research or otherwise disclose patient or subject identities in any manner. Baseline Assessment: Subjects who meet eligibility criteria during the phone screening procedures and give verbal consent will participate in a baseline assessment. All assessments (baseline/ 6- /12-month f/u) will be completed by a blinded independent evaluator (IE) over the phone. Baselines will begin with a socio-demographic survey, followed by the PHQ-9 and a myriad of other measures (see HOPEIIR Baseline and Follow Up Measures document in Sect S). A1c collection will be coordinated by IEs. Lab collection is feasible, with high completion rates in our prior VA studies. In EPIC, A1c collection was higher than survey collection rates. All participants who do not meet the final A1c eligibility criteria but were identified as having significant depressive symptoms will be notified of their results, and a note will be placed in their medical record indicating this finding to their PCP. Enrolled participants will also have a note placed in their medical record indicating the presence of clinically significant depressive symptoms and the results of their most recent A1c labs. The participant will be provided with materials on diabetes and depression, and the participant and PCP will be given evidence-based recs for treatment of the depressive symptoms. After baseline, participants will receive \$30. Measures will be repeated from the baseline assessment at 6 and 12-mos., but no demographics. If staff cannot reach a veteran 3x by phone to schedule f/up, a letter may be sent. Packets will be mailed to participants as a courtesy for each assessment so that they may follow along with the measures as they are administered by phone (Sect S). Randomization: All consented participants who complete the baseline and are eligible after baseline and blood draw will be randomized to HOPE or Enhanced Usual Care. Eligible participants at each site will be randomly assigned by a RA following the baseline evaluation. In accordance with VA policy and procedures, participants randomized to the HOPE intervention will receive VHA Form 10-3203 (Sect S) with

their intervention materials in the mail. Participants randomized to HOPE will be instructed to complete the consent for voice recording form and return it in a pre-provided postage paid envelope. Randomization will be blocked and stratified by site to assure balance in the number of patients assigned to HOPE or EUC at each facility. Within each site, we will use random blocks of 4 and 6. The random numbers will be generated in SAS PROC PLAN by [name]. The number of patients randomized at each site will be proportional to the number of patients estimated to be eligible for the study at that facility and adjusted as new CBOCs open and their data becomes available. Should a proportional recruitment prove difficult, we will reconsider this practice to ensure that we meet our sample size goals. Conducting EUC: All enrolled participants will receive the EUC procedures at their clinical site pertaining to diabetes care and depressive symptom management. Once participants are consented and enrolled, study personnel will: 1-Send a standardized letter to study participants notifying them of the study findings related to their diabetes A1C levels and depressive symptoms, and a reminder that their PCPs will be notified as per the informed consent (in Sect S as EUC Cover Letter). Patients will also be provided with basic educ. materials related to diabetes and depression (Sect S); 2-Enter a parallel note in the patient's CPRS record notifying the PCP of these findings, with an add'l signer request (to signify awareness of note); 3-Include recs for MH referral or treatment prompt for depression in the CPRS note; Repeat steps 1-3 after the results of the 6mo and 12mo data collection are available. No specific recs for diabetes care will be provided, no further contact will be made during the acute intervention period for participants in EUC. Conducting HOPE Intervention: Study RAs will contact participants randomized to HOPE to arrange the first behavioral call w/in a 2-3 week window. The coach will initiate calls at the participant's time and day of choosing. If a veteran fails to appear 3x for the phone appt, a letter may be sent by the staff on behalf of the coach. Like EUC, HOPE patients will receive basic educ info on diabetes and depression. A standardized behavioral counseling framework is used by coaches to guide each of the calls, regardless of the specific contents of each session. At the conclusion of each behavioral coaching call, the coach will summarize the progress of the current session and schedule the next call. The coach will then enter a note in the participant's CPRS record with the participant's PCP listed as an additional signer. This note will summarize the specifics of what was discussed during the prior coaching call and provide, in the participant's own language, the agreed upon specific goal and action plan(s). Coaches may also suggest additional f/u or referrals to the PCP, based on the participant's needs and requests, such as a referral to a diabetes educator or nutritionist. Coaches may also ask PCPs to schedule a quicker (urgent care) f/u visit if warranted. The actual request for referrals and all medical f/u appts and medication changes will be left to PCPs' discretion. HOPE Intervention modules: A total of 9 sessions will be conducted during a 6mo period. For the first 3mo, coaching sessions will be 30min, take place bi-weekly, and will include 2 core sessions and 4 elective sessions (where patient chooses topic to cover). In the next 3mo, 3 f/u sessions, each 15min long, will occur once a month. There are a total of 6 modules for the patient to choose from for their elective sessions, and modules may last more than one session. The modules assigned to elective sessions 3-6 are adaptable, and one or more may be presented in any order at the participant's and coach's discretion.

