
## Section G: Sample Size/Data Analysis

### G1. Sample Size

How many subjects (or specimens, or charts) will be used in this study?

Local: 455      Worldwide: 455

Please indicate why you chose the sample size proposed:

The proposed sample size of 455 includes 425 patients and 30 clinicians.

The sample size of clinicians was determined by creating a schedule for the expected flow of Veteran participants in the study that predicts expected demand for coaching.

In determining the sample size of patients for the study, we examined the number of patients needed to have adequate power for both hypotheses related to the primary aim (specific aim 1). The sample size determined for the primary aim was inflated to account for potential correlation of patients treated by the same PCP and to account for attrition at 1 year of 25%, based on our and other prior VA studies.

The sample size is based on testing for a clinically important difference between the two groups at a single time point, using a two-group t test with a 0.05 two-sided significance level and power of 80%. For HbA1C, a difference of 0.5 is considered clinically significant within a 6-month time frame. Using a difference score of 0.5 in the mean HbA1c between the two groups and an estimated pooled standard deviation of 1.1 results in

an effect size,  $d = .45$ . This effect size is consistent with our prior RCT study on behavioral coaching interventions which generated HbA1c level differences of 0.68 and a medium effect size of 0.50 and estimates from our HOPE pilot confirm these effects. Using these data, a sample size of 79 per group or 158 total would be needed for a significant difference in the proportion of participants achieving greater than or equal to 0.5 improvement in HbA1c.

For PHQ-9, a score of less than 10 or a 5-point decline from baseline would be considered a clinically significant improvement. The sample size of 79 per group would have 80% power to detect a change as small as 1.5 points in the PHQ-9 score with a two-sided  $\alpha = 0.05$ . From our own work using cognitive-behavioral therapy for medically ill Veterans with depression, we found clinically significant improvements in Beck Depression Scale scores consistent with effect sizes of 0.98 at 8 weeks and 1.05 at 20 weeks post-intervention. This level of efficacy is consistent with our estimates of clinically significant change as indicated by PHQ-9 scores.

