Following the approach of Schnurr et al, we inflated the sample size to account for a correlation among patients seen by the same PCP using the formula,  $f = 1 + (m - 1)\bar{r}$ , where  $m$  is the average number of patients per provider and  $\bar{r}$  is the intra-class correlation coefficient. Assuming there will be 40 to 50 PCPs results in  $m = 4$  and estimating  $\bar{r}$  as .05 yields  $f = 1.15$ . This inflation factor is modest but reasonable, given the nature of the study and the extent of the external clinical providers' involvement (supported by personal communication with [name] – May 2010).

Thus, the sample size needed for analysis is 182 total (91 per group). Finally, adjusting this for 25% attrition using the inflation factor of 1.33 [i.e.,  $1/(1-.25)$ ] gives a total of 242 patients to be recruited. Therefore, a final cohort of 182 at 12-month follow-up (i.e., recruitment of 242 to allow for 25% attrition) would provide sufficient power to conduct analyses for Aim 1. This sample would provide 80% power to detect an effect size of 0.45, which represents a difference in HbA1c of 0.5 with a standard deviation of 1.1 and a difference in PHQ-9 scores of as little as 1.5 with standard deviation of 3.4.

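### The protocol states 60:40 allocation (146 HOPE, 96 EUC), but its block scheme reads as 1:1 and its sample size and 80% power are derived for equal groups

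*Protocol*

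**What the plan says.** Three parts of the protocol fix the size of the arms.

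- **Section F1 (Design)** sets an unequal split of 242 patients: "60% of the participants (n=146) will be randomized to receive 9 behavioral coaching sessions in 6 months" and "the other 40% (n=96) will receive EUC".
- **Section F2 (Procedure, randomization)** states: "Randomization will be blocked and stratified by site to assure balance in the number of patients assigned to HOPE or EUC at each facility". It adds: "Within each site, we will use random blocks of 4 and 6". It does not say how many patients in a block go to each arm.
- **Section G1 (Sample Size)** starts from 79 per group, "using a two-group t test with a 0.05 two-sided significance level and power of 80" percent. It inflates this for patients sharing a primary care provider and concludes: "Thus, the sample size needed for analysis is 182 total (91 per group"). It then inflates for attrition to 242. The section does not mention unequal allocation.

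Section J1 (Waiver of Consent) notes that enrolment has stopped, so the allocation list already exists.

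**The concern.** As naturally read, these statements do not describe one trial. A statistician following F2 and G1 would build a 1:1 list. One following F1 would build a 3:2 list. A reader of the results could not tell which arm sizes were planned, or whether an observed imbalance was intended or was a fault in the randomization. The 80% power in G1 is also attached to a total that F1 then splits differently, so the stated power and the stated arm sizes do not belong together.

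**Working it through.** **Inputs.**
- F1: 146 HOPE and 96 EUC, total 242.
- F2: block sizes 4 and 6, stratified by site.
- G1: two-sided alpha 0.05, power 80%, t test; HbA1c difference 0.5 with SD 1.1, taken as d = 0.45 (0.5/1.1 = 0.4545); PHQ-9 difference 1.5 with SD 3.4 (d = 0.441); m = 4 patients per provider; intraclass correlation 0.05; attrition 25%.

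**1. The plan's own figures, at 1:1.**
- At d = 0.45 the t test needs 78.5, so 79 per group (158 in total). Power with 79 per group is 80.3%.
- Clustering factor: 1 + (4 − 1) × 0.05 = 1.15. Then 79 × 1.15 = 90.85, so 91 per group and 182 in total.
- Attrition: 182 × 1.33 = 242.06, so 242.

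The chain reproduces, with equal groups at every step. Half of 242 is 121 per arm.

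**2. Do the blocks fit 60:40?**
- 146/242 = 60.3%.
- 60% of 4 is 2.4 and 60% of 6 is 3.6. Neither is a whole number, so no single block of either size is 3:2. A constant 3:2 needs a multiple of 5.
- Blocks of 4 and 6 fit 1:1 directly, as 2:2 and 3:3.
- Under 1:1 blocks, the arm difference at a site never exceeds 3 (half of a block of 6). The gap in F1 is 146 − 96 = 50, and 50/3 = 16.7. At least 17 sites, all at the maximum in the same direction, would be needed to reach it.
- A mix could average 60%. One 2:2 block and one 4:2 block give 6 of 10 to HOPE; so do 3:1 with 3:3. In the first mix the HOPE share is 50% in fours and 67% in sixes, so a site that fills only a few blocks need not be near 60:40.

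**3. Size of the discrepancy.** 146 − 121 = 25 more patients in HOPE and 121 − 96 = 25 fewer in EUC.

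**4. Power if the list was 146:96.**
- Analysed after 25% attrition: 146 × 0.75 = 109.5 and 96 × 0.75 = 72. EUC would have 72, against the 91 per group that G1 says is needed.
- Effective size after clustering: 109.5/1.15 = 95.2 and 72/1.15 = 62.6. At 1:1 it is 91/1.15 = 79.1 per group.

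| Outcome | d | Power at 1:1 | Power at 146:96 |
|---|---|---|---|
| HbA1c, rounded d | 0.45 | 80.3% | 78.5% |
| HbA1c, 0.5/1.1 | 0.4545 | 81.1% | 79.3% |
| PHQ-9, 1.5/3.4 | 0.441 | 78.8% | 76.9% |

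The loss due to allocation is 1.8 to 1.9 points in each row. PHQ-9 is below 80% even at 1:1 (78.7% with exactly 79 per group), so most of its shortfall from 80% at 146:96 is not due to the split.

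For scale only: 80% power at a 3:2 split would need about 163.4 × 1.15/0.75 = 251 recruited at d = 0.45, or about 160.2 × 1.15/0.75 = 246 at d = 0.4545.

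**The case against.** **A reader might infer that the block scheme cannot deliver 60:40 at all.** The protocol does not support that. F2 gives block sizes and not block composition, and composition may properly sit in a separate randomization specification. Unequal blocks of 4 and 6 can average 60:40, as shown above. What stands is narrower. No such scheme is described, it would vary the allocation probability from block to block, and it would not hold the ratio at small sites, although control at each facility is the stated reason for blocking. The phrase "to assure balance in the number of patients assigned to HOPE or EUC at each facility" most naturally means equal numbers. If it were read as adherence to the planned ratio, whole blocks of 4 and 6 would still not contain 3:2.

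**A reader might also infer that the trial is materially underpowered.** That does not follow.
- The loss is under 2 points, and at the unrounded HbA1c inputs power is 79.3%.
- The figures come from an unadjusted t test, whereas the models in G2 adjust for the baseline value. If the baseline-to-follow-up correlation were 0.3 to 0.6 (an assumption; the protocol gives none), power at 146:96 and d = 0.45 would be roughly 82% to 93%, with the 1.15 factor kept.
- Patients are randomized individually, so a provider can have patients in both arms and the 1.15 factor may be conservative. Without it, 109.5 against 72 gives 83.9%.

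Finally, unequal allocation is legitimate, no bias is shown, and the planned models adjust for site. All of this limits the consequence. None of it removes the conflict between the stated ratio, the stated purpose of blocking and the stated group sizes.

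**Conclusion.** The allocation is stated inconsistently: 146:96 in F1, and by natural reading about 121:121 in F2 and G1, a difference of 25 patients per arm. The total of 242 and the 80% power reproduce only for equal groups. If the trial was allocated 60:40, t-test power under the protocol's own 25% attrition and 1.15 inflation is about 78.5% at d = 0.45 (79.3% at 0.5/1.1) for HbA1c and about 77% for PHQ-9. Of these shortfalls, only about 1.8 points come from the allocation.

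The finding concerns a core design fact that is contradictory as written; the power is a secondary correction. It rests on reading balance in F2 as equal numbers, and on F2 describing no unequal block composition. The protocol does not show which list was used, so it cannot be said which section is in error.

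**What to change.** State in the protocol the allocation ratio and the block composition of the list actually used, and align F1, F2 and G1 with it. Prescribing new block sizes would serve no purpose now that recruitment has ended.

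- **If the list was 60:40:** say in F2 how the blocks of 4 and 6 were composed, and replace the wording about balance with the intended ratio. In G1, replace 91 per group with about 109 HOPE and 72 EUC analysed. Restate power as about 78.5% at d = 0.45 (79.3% at 0.5/1.1) for HbA1c and about 77% for PHQ-9 at 1.5/3.4, noting that PHQ-9 was already about 78.7% at 1:1.
- **If the list was 1:1:** correct the percentages and the 146 and 96 in F1 to equal arms of about 121.

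The cost is wording and, in the 60:40 case, a slightly lower stated power. No extra patients are needed and conduct does not change.
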